## Abstract

**Background:**

Locomotive syndrome (LS) is a condition in which muscle weakness and reduced motor function due to musculoskeletal disorders cause reduced mobility and physical function. In Japan, musculoskeletal disorders are the most frequent reason for requiring home support or nursing care, and the prevention and amelioration of LS are thus being emphasized. However, it is difficult for older people to make a habit of exercise therapy, which is the mainstay of LS treatment. We investigated whether digital therapy could (1) lead to behavioral change in older people and (2) prevent or improve LS in older people.

**Objective:**

We sought to determine whether digital therapeutics (DTx) are useful for the prevention and amelioration of LS in older people, and we assessed the effects of DTx on the participants’ exercise awareness and motor function.

**Methods:**

We conducted a multicenter, prospective, longitudinal, nonrandomized, single-group study of Japanese adults aged ≥40 years who were eligible for LS checks. Each participant underwent an 8-week locomotion training (LT) intervention, and their subjective and objective motor abilities and motor awareness were objectively assessed at the following time points: baseline (before the start of the DTx), interim (4 weeks after the start of the DTx), and end (8 weeks after the start of the DTx). We evaluated the participants’ objective motor function using the timed up and go (TUG) test, and we compare the results using a 3-way ANOVA with the TUG test at the 3 evaluation time points as the dependent variable. The results of the 25-question Geriatric Locomotive Function Scale, which is a subjective measure of motor function, and the results of the Behavioural Regulation in Exercise Questionnaire 3, which assesses motor awareness, were also evaluated using an ANOVA in the same way as the TUG test. The significance level was set at .05 / 3 = .0167 after Bonferroni correction.

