#### Primary Outcome

The primary outcome is TUG test values before and after the DTx intervention. The TUG test is widely used in clinical practice as an outcome measure to assess mobility, fall risk, and dynamic balance in adults, and it can assess objective mobility [21,22]. Furthermore, previous research has shown that patients with LS have significantly longer TUG times than control groups [23]. In patients with rheumatoid arthritis, TUG values are significantly shortened and physical function is improved by continuing LT [24]. We determined that TUG is a useful indicator of the effects of LT for participants with LS.

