### Statistical Methods and Sample Size

The primary outcome of this study, TUG test values, will be measured repeatedly in the same participants at 0 weeks before the DTx intervention and 4 and 8 weeks after the intervention. These data will be compared with an ANOVA, with the TUG score as the dependent variable. The secondary outcomes, GLFS-25 and BREQ-3 scores obtained at the 3 time points, will also be compared with an ANOVA. The significance level will be set at .05 / 3 = .0167 with Bonferroni correction.

The minimal clinically important difference in the TUG test for patients with degenerative disc disease has been reported to be 3.4 (SD 5.0) [26]. Considering this finding, we set the minimal clinically important difference at 3 for this investigation. The required sample size was calculated using G*power (Heinrich-Heine-Universität Düsseldorf) [27]. We selected the corresponding *t* test, and we calculated the effect size as 0.6 based on a mean difference of 3.0 and an SD of difference of 5.0. Assuming that α is .05 and power (1 − β) is .80, the required sample size was estimated to be 24. We set the target number of cases for this study at 50, taking into account that the SD might be smaller than in previous studies, some participants might drop out, and other factors.

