### Randomization and Blinding

This is a nonrandomized (unblinded) study and will use a single group. All participants will serve as their own controls; data from all participants before the DTx intervention will be used and compared with the data from after the DTx intervention. The planned statistical methods will add strength to the study’s conclusions.

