## Results

Trial enrollment began in April 2024 and will initially continue until at least April 2025. As of April 2025, 47 had participants agreed to be evaluated, 47 participants had completed the interim evaluation, and there were complete data sets from 45 participants for the proposed analysis. The data analysis has not yet been conducted.

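### The primary TUG analysis is misnamed and inconsistently stated, and no deciding before–after contrast is fixed

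*Protocol article*

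**What the plan says.** The primary method is named twice in the protocol article.

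- Abstract, Methods: "we compare the results using a 3-way ANOVA with the TUG test at the 3 evaluation time points as the dependent variable". The two questionnaires are to be analysed in the same way.
- Statistical Methods and Sample Size: "These data will be compared with an ANOVA, with the TUG score as the dependent variable".

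Other sections describe what is being compared.

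- Primary Outcome: "The primary outcome is TUG test values before and after the DTx intervention".
- Statistical Methods and Sample Size: TUG "will be measured repeatedly in the same participants at 0 weeks before the DTx intervention and 4 and 8 weeks after the intervention".
- Randomization and Blinding: "All participants will serve as their own controls; data from all participants before the DTx intervention will be used and compared".
- Sample size, same section as the ANOVA: "we calculated the effect size as 0.6 based on a mean difference of 3.0 and an SD of difference of 5.0", with alpha .05, power .80 and a required number of 24. The target is 50.
- Significance level: "The significance level will be set at .05 / 3 = .0167 with Bonferroni correction". The three comparisons behind the divisor are not identified.

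**The concern.** A 3-way ANOVA has three factors. This is a single-group study, and the only factor described is time, at 0, 4 and 8 weeks. The abstract's label is therefore wrong, and it differs from the label in the methods section. Neither place names a repeated-measures ANOVA, a participant effect or a mixed model, although the sample size depends on within-person differences.

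The second problem remains even if the model is read charitably. With two follow-up visits, a before–after outcome can mean week 4, week 8 or any difference among the three visits. An omnibus time test answers only the last of these. It can be positive with no benefit at the end of the 8-week intervention. Leaving the choice open also allows the deciding time point to be picked after the results are seen, in a study with no control group.

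**Working it through.** **Inputs from the article.** Mean difference 3.0 s; SD of the difference 5.0 s; alpha .05 for sizing and .05/3 = .0167 for analysis; required n 24; target 50; 45 complete data sets as of April 2025.

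**Assumptions, not in the article.** Equal variances and equal correlations across visits; normal data; a linear course of 0, −1.5, −3 s for the power figures; within-person correlation ρ of 0.5 to 0.9.

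**1. Reproduce the plan's figure.** The standardised paired effect is 3.0/5.0 = 0.6. For a two-sided paired t test, the noncentrality is 0.6·√n. At n = 24 this is 0.6 × 4.899 = 2.94 against a critical t(23) of 2.07, which gives power 0.804. So 24 is reproduced exactly, and the sizing does rest on pairing.

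**2. Paired 8-week contrast at the analysis level.** The same formula at alpha .0167 gives:

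| n | Power at .05 | Power at .0167 |
|---|---|---|
| 24 | 0.804 | 0.641 |
| 45 | 0.976 | 0.933 |
| 50 | 0.986 | 0.958 |

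For 80% power at .0167, n = 32, still below the target of 50.

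**3. Repeated-measures omnibus test.** The within-person error variance is 5²/2 = 12.5. The noncentrality is λ = n·Σ(mₖ − m̄)²/12.5, on 2 and 2(n − 1) degrees of freedom.

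- Course 0, −1.5, −3: the sum of squares is 1.5² + 0 + 1.5² = 4.5. At n = 45, λ = 45 × 4.5/12.5 = 16.2. Power at .0167 is 0.889.
- Course 0, −3, 0 (gain at week 4, none at week 8): the mean is −1 and the sum of squares is 1 + 4 + 1 = 6. At n = 45, λ = 45 × 6/12.5 = 21.6. The test is significant with probability 0.965 (about 96% in simulation). In the same simulated trials, the paired 8-week contrast rejects in 1.5 to 2%, its nominal level.

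The omnibus test is thus somewhat more likely to be positive when the gain has vanished by week 8 than when it builds steadily to 3 s.

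**4. Only if no participant term is fitted.** Holding the SD of the difference at 5, the SD at each visit is 5/√(2(1 − ρ)), and between-person variance enters the error term. Simulated at n = 45, alpha .0167, course 0, −1.5, −3:

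| Assumed ρ | SD per visit (s) | Ordinary ANOVA | Repeated-measures ANOVA |
|---|---|---|---|
| 0.5 | 5.00 | about 52% | about 89% |
| 0.7 | 6.45 | about 15% | about 89% |
| 0.8 | 7.91 | about 2% | about 89% |
| 0.9 | 11.18 | below 0.1% | about 89% |

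The first ordinary-ANOVA figure varied from 51 to 53% between simulation runs. With no true change, the ordinary ANOVA rejects in under 0.1% of trials instead of 1.67%.

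**The case against.** The strongest reply is that ANOVA is a family that includes the repeated-measures form. The sentence just before the methods statement says the same people are measured repeatedly, participants are described as their own controls, and the sizing is paired. A reader might infer from the labels alone that the plan throws the pairing away. The text does not support that: it points to a within-person analysis with a missing qualifier and a wrong label. The power losses in step 4 therefore describe a misreading that the wording permits, and they also depend on a correlation the article does not give. With the pairing kept, the study is well powered for its stated effect.

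It can also be said that .05/3 may stand for the three pairwise time comparisons, which would include week 8 against baseline. That is possible. It could equally mean the three outcome measures, and the article does not say. Even on the first reading, three comparisons would be tested with none named as the deciding one.

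Three further inferences are tempting and are not supported.

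- **A complete-case rule.** The Results section says "there were complete data sets from 45 participants for the proposed analysis". This is a status count, not a rule on who is analysed, and handling of missing data may properly sit in a fuller document.
- **Dropout between weeks 4 and 8.** All 47 had the interim evaluation and 45 had complete data, but the abstract says participation was ongoing. The other two may simply not have reached week 8.
- **Finished data collection.** Enrolment was to run until at least April 2025, and 47 had been enrolled against a target of 50.

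None of this removes the wrong label, the disagreement between the two statements or the missing deciding contrast.

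**Conclusion.** The point holds in this form: the primary method is wrongly named in the abstract, incompletely named in the methods section, and not tied to a deciding time contrast.

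The contrast is the weightier part, because it does not depend on how ANOVA is read. The 96% figure rests on n = 45, an SD of difference of 5 s between any two visits, and a deliberately chosen course in which the 3 s gain at week 4 is lost by week 8. It shows what the omnibus test can do; it does not forecast this trial. The fall from 89% to about 52%, 15% or 2% applies only if the participant term is left out, at assumed correlations of 0.5, 0.7 or 0.8.

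Because the wording defines the primary result, it should be settled before the data are analysed.

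**What to change.** Use the same statement in the abstract and in Statistical Methods and Sample Size, for example:

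*TUG at 0, 4 and 8 weeks will be analysed with a one-factor repeated-measures model, with time as a three-level categorical effect and a participant effect. The primary estimate is the mean change from baseline to 8 weeks with its confidence interval. The 4-week change is supportive.*

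A repeated-measures ANOVA with this named contrast is enough to cure the wording. A linear mixed model with categorical time is preferable because it also keeps participants who miss one follow-up visit.

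State which three comparisons the .0167 level covers. If it applies to the primary TUG contrast, restate the sample size at that level: 32 in place of 24, which the target of 50 already exceeds.

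The cost is a wording change, with no new data and no larger sample. The Results section reports that analysis had not been done as of April 2025. The change should be made and dated before it starts, since a contrast named afterwards would look chosen from the results.

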**Results:**

As of April 2025, this study had enrolled 47 participants, and complete data had been gathered from 45 participants for the proposed analysis. Study participation was ongoing as of April 2025.

**Conclusions:**

The study cohort will be used as a basis for further observational and intervention studies. This research could lead to more efficient use of medical resources and a reduction in financial and medical burdens on individuals and the economy, and it could support the prevention and amelioration of LS and the establishment of exercise habits among older people.

**Trial Registration:**

University Hospital Medical Information Network Clinical Trials Registry UMIN000053922; https://center6.umin.ac.jp/cgi-open-bin/ctr_e/ctr_view.cgi?recptno=R000061550

**International Registered Report Identifier (IRRID):**

DERR1-10.2196/70163

## Introduction

### Background and Rationale

The Japanese Orthopaedic Association (JOA) issued its first guidelines regarding locomotive syndrome (LS) in 2007 [1]. Locomotive syndrome refers to a condition in which a musculoskeletal disorder results in muscle weakness and motor weakness, leading to reduced mobility and physical function [1]. The development of LS causes a decline in healthy life expectancy and can lead to individuals becoming bedridden and requiring long-term care [2]. In Japan, motor system disorders are the most frequent reason for requiring assistance at home or nursing care, accounting for 24.8% of all cases [3]. The JOA recommends the early detection of motor function decline by conducting LS checks (LSCs), in part to prevent the future need for assistance or care [4]. The JOA also advocates locomotion training (LT), which involves standing on one leg and squatting, to prevent and ameliorate LS [5].

Guidelines for assessing the risk of LS were developed in 2015 [6]; these defined stage 1 LS as the early stage of motor decline and stage 2 LS as advanced motor decline. In 2020, stage 3 LS was added, defined as a state of progressive decline in mobility and difficulty in social participation [7]. The risk of developing LS is assessed based on three items: (1) a stand-up test, (2) a 2-step test, and (3) the 25-question Geriatric Locomotive Function Scale (GLFS-25) [5].

Japan has one of the world’s most prominent aging populations, and the burden of health care for the oldest segment of Japan’s population on the country’s insurance system continues to increase [8]. It is also necessary to consider how to make the most effective use of limited medical resources. The prevention and amelioration of LS are considered important as countermeasures against motor system disorders. Exercises such as LT are effective for preventing and ameliorating LS [5], but it is difficult for many older adults to start or continue an exercise routine. As one solution, we advocate an approach to the prevention and improvement of LS in older people based on using technological devices to promote behavioral change.

Technology is used in the medical field for electronic medical records, telemedicine, and surgical robots; in addition to this, mobile devices are used for medical procedures and support, which is called mobile health (mHealth) [9]. Digital therapeutics (DTx) are an area of mHealth that is receiving particular attention [10]. A variety of apps have been approved by insurance as DTx, including diabetes and hypertension self-management apps and smoking cessation support apps [11-13]. However, DTx for musculoskeletal diseases have not been approved for insurance coverage. Although some apps have functions such as step counting and exercise management, they are not scientifically supported. We have created a smartphone app for older people who have no exercise habits and whose physical functions have declined. The smartphone app has functions that support the implementation of 2 types of LT, using video and audio, and when participants carry out LT, the implementation status is recorded not only on the target person’s smartphone, but also on the health care provider’s smartphone. The advantage of this system is that health care providers can check the progress of LT remotely, and the patient can feel that they are exercising with the support of health care providers. We are conducting this study to determine whether the use of DTx can lead to behavioral change in older people and prevent or improve LS.

### Objectives

The study’s primary aim is to determine whether the use of a smartphone app (ie, DTx) can prevent or ameliorate LS in older people: the outcomes are exercise awareness as assessed by the Behavioural Regulation in Exercise Questionnaire 3 (BREQ-3) and motor function as assessed by the GLFS-25 and timed up and go (TUG) test. In this study, participants who were unable to perform the stand-up test or 2-step test due to hip or knee pain were excluded from the measurement items. The research questions are as follows: (1) Can older people use DTx to proactively change their exercise habits with the help of their health care providers? (2) Are changes in exercise habits in older people associated with changes in motor awareness and function?

Our main and secondary study hypotheses are that (1) continued LT with DTx will prevent or improve LS in older adults and (2) well-established exercise habits will improve these individuals’ motor awareness and function.

## Methods

### Participants and Study Setting

We plan to recruit a minimum of 50 participants aged ≥40 years who are eligible for LSCs [14] at any of 3 general hospitals (Bange-Kosei General Hospital, Southern Tohoku General Hospital, and Minami-Soma City General Hospital) that perform orthopedic surgery. The target minimum numbers of participants is 25 at Bange-Kosei General Hospital, 15 at Southern Tohoku General Hospital, and 10 at Minami-Soma City General Hospital. The overall recruitment target is based on the minimum sample size necessary to complete the intended analysis, taking omissions into account.

The study’s inclusion criteria are as follows: participants aged ≥40 years who generally have lower-extremity muscle weakness [15] and who have visited 1 of the 3 abovementioned hospitals for an LSC, which are scored as follows: 1 point if the individual cannot put on a sock on one foot; 2 points if they stumble in their house; 3 points if they need a handrail to climb stairs; 4 points if they have difficulty using a vacuum cleaner at home; 5 points if they have difficulty carrying parcels weighing >2 kg; 6 points if they have difficulty walking continuously for >15 minutes; and 7 points if they cannot cross a crosswalk with a green light. Additional inclusion criteria are scoring ≥3 points on the Mini-Cog cognitive functional assessment [16,17], having access to the smartphone app, and being able to provide informed consent for study participation. The exclusion criterion was difficulty using smartphone apps due to cognitive decline or visual or hearing impairment.

### Study Design

This trial is a multicenter, prospective, longitudinal, nonrandomized, single-group study of Japanese adults aged ≥40 years with applicable LSC results. The design includes 3 evaluation time points: baseline (0 weeks, ie, before the initiation of DTx), an interim evaluation (4 weeks after DTx initiation), and a final evaluation (8 weeks after DTx initiation).

An investigation of DTx that was designed to reduce anxiety about recurrence in postoperative breast cancer patients included a baseline assessment before the DTx intervention, an interim assessment after 4 weeks of intervention, and a final assessment after 8 weeks of intervention [18]. Previous studies have shown that 6 weeks of balance exercise intervention and 2 months of body weight–bearing exercise can improve lower limb muscle strength, balance ability, and walking speed in older people [19,20]. We and other research groups thus consider 4-week and 8-week postintervention assessment time points as appropriate for this type of study.

We registered the trial with the University Hospital Medical Information Network Clinical Trials Registry (UMIN000053922; receipt number R000061550). The date of approval was March 22, 2024.

### Procedures

#### Recruitment

Participants will be recruited from among patients attending the collaborating hospitals. All 3 recruitment sites follow the same recruitment plan. Recruitment will continue until the target number of cases is achieved, with a 1-year time limit. At the end of a regular outpatient clinic session, a participant who meets all of the eligibility criteria and wishes to participate in the study will be provided with a description of the study, a questionnaire, and an evaluation sheet, and they will be asked to give their written informed consent to participate in the study. The need for follow-up and written consent for future contact will also be explained. The candidate participants are also informed that they can withdraw their consent or participation at any time if they so desire.

#### Intervention

The smartphone app used in this study is a newly prototyped app developed for this research study. We will provide smartphones equipped with a communication environment and downloaded apps in advance, which will be lent to the participants (Figure 1). The participants will be instructed to refrain from using the smartphone for any purpose other than use of the relevant smartphone app.

**Figure 1 figure1:**
[figure not shown]
Implementation schema for the locomotive training (LT) app used in this study. The physician in charge will provide a smartphone onto
which the LT app has been downloaded to the patient. The patients perform the LT at home, and the app’s implementation data are stored in the database
and saved in the cloud. Through the cloud, the physician can check the participant’s LT implementation remotely.

Each participant will be scheduled for LT intervention every day for 8 weeks. The LT application is simple to use and is set up so that by touching the screen, a voice announcement is played and the user can perform 2 LT programs: the 1-leg stand program and the squat program. A single LT session consists of a program of 60 seconds of standing on one leg and 5 squats, with each exercise repeated 3 times. For participants with weak legs and backs who find it difficult to do the regular LT, it is recommended that they stand on one leg while supporting their body with their hands and fingers on a desk, or that they sit on a chair and stand up by putting their hands on a desk instead of doing squats. In addition, for participants with particularly weak legs and backs, each LT repetition could also be reduced to 1 time instead of 3 times [5]. Sustainable goals are set for each individual for LT continuity. After completion of the LT, the participant touches the screen to check the record of the LT, not only on the participant’s but also on his or her physician’s smartphone (Figure 2).

